#### 4.5 Usability

We define usability as the degree to which the KK2.0 can be used easily, efficiently, and with satisfaction/low user burden by the stakeholders [42]. For this experiment, KK2.0 naïve participants (having no previous exposure or experience with the system) will receive practical training in the use of the KK2.0 system, which includes three steps, namely the set-up, the scanning, and the AI verification process.

The practical training consists of an initial demonstration of this three-step process and a walk-through of system user manuals. Afterwards, the participants will be invited to two natural use environments, either to a laboratory setting, or a field setting. The participants will be organized into four groups per setting, each consisting of two participants per group, resulting in a total of 16 participants. This grouping reflects a planned real-life group setup, wherein the involvement of two laboratory technicians is expected to carry out the tasks. The group will be asked to perform the set-up as a team. The two following steps, the scanning and verifying AI, will be performed individually. For this, participants will be asked to each process 6 slides with KK2.0. Each slide will be processed in following order, whereby the participant’s effort will be increased: (1) the results are available soon after scanning is complete (e.g., KK2.2 results), (2) the user must perform the simple verification procedure before the results are available, (3) the user must perform the complete verification procedure before the results are available. During the three-step task performance, participants will verbalize their experiences and detect weak points in their interaction with the scanner (i.e., think–aloud protocol [43]). The whole session will be video-recorded, and data will be generated by verbatim transcriptions, and an observation checklist for collecting comparative metrics (e.g., task completion time and both error and success rates). Following, a semi-structured interview will be implemented to capture the ease-of-use/ease-of-learning, efficiency, and satisfaction/low user burden, as well as potentially missed barriers and facilitators during the task completion process. The interviews will be conducted by one investigator and structured around four sections: the background of the participant; the training; the KK2.0; the context. The data will be audio-recorded and transcribed verbatim.

### 5 Sample size calculation

A formal sample size calculation was conducted for the experiments on the diagnostic performance (**section 4.1**), and the repeatability and reproducibility (**section 4.2**). For the other experiments we did not determine the sample size, because either no hypothesis was defined as the outcomes will feed into another experiment (**section 4.3 Time-to-result**), the hypothesis is based on a simulation study (**section 4.4 Cost efficiency**), or the sample size was based on common practice in literature (**4.5. Usability**). In the following sections we will only briefly discuss the applied methodology to determine the sample size for the three experiments (diagnostic performance, repeatability/reproducibility, and usability). For a detailed description of the applied methodology for the first two experiments we refer the reader to **S3 File.** The required sample size for these two experiments on diagnostic performance and repeatability/reproducibility are summarized in **Table 4**.

**Table 4 pone.0309816.t004:** Overview of the required number of KK thick smear to test the hypotheses for the experiments on diagnostic performance and repeatability/reproducibility.

Experiment	Hypothesis	Intensity of infection	Number of KK thick smear			
			Any STH	*Ascaris*	*Trichuris*	Hookworm
** *Diagnostic performance* **						
	***H1*.*1*:** the clinical sensitivity of KK2.0 to detect low intensity infections is non-inferior to that of KK1.0 for *Ascaris*, *Trichuris* and hookworms	Low	_	125	180	140
	***H1*.*2*:** the clinical sensitivity of KK2.0 to detect MHI infections is non-inferior to that of KK1.0 for *Ascaris*, *Trichuris* and hookworms	MHI	_	110	145	>350
	***H1*.*3*:** the clinical specificity of KK2.0 to detect any intensity infections is non-inferior to that of KK1.0 for *Ascaris*, *Trichuris* and hookworms	No infection	_	225	225	225
	***H1*.*4*:** the clinical specificity of KK2.0 to detect MHI infections is non-inferior to that of KK1.0 for *Ascaris*, *Trichuris* and hookworms	Low	_	165	165	165
** *Repeatability and reproducibility* **						
	***H2*.*1*:** the repeatability and the reproducibility of the scanner set-up process is at least 99%	All	90	_	_	_
	***H2*.*2*:** the repeatability and the reproducibility of AI verification process is at least 99%	All	90	_	_	_
	***H2*.*3*:** the repeatability and the reproducibility of KK2.0 is at least 99%	All	90	_	_	_

#### 5.1 Diagnostic performance, repeatability, and reproducibility

Generally, we opted to conduct a series of simulation studies over the standard sample size methodologies, as this approach allowed us (i) to better capture the variation in test results that are otherwise difficult to account for (e.g., clinical sensitivity of KK1.0 increases as a function of egg numbers in a slide), and (ii) to ensure that the sample size calculation and the final interpretation of the field data are both based on the same statistical approach (e.g., the relative position of confidence intervals (CI) to predefined set of values; see also **Fig 5**). In brief, each of these simulation studies consists of a series of in-silico experiments that are iterated under different conditions (e.g., different sample sizes). Based on this iterative process, we determined the lowest sample size that allowed for confirming the hypothesis in at least 80% of the iterations (= power).

**Fig 5 pone.0309816.g005:**
[figure not shown]
Overview of the different outcome scenarios based on a random sample and its corresponding CI. This figure illustrates the different outcome scenarios around the difference in performance between KK2.0 and KK1.0 based on the CI. The green lines represent the scenarios where there is evidence of non-inferiority, while the lines in orange illustrate the scenarios where there is no evidence of non-inferiority. In this example we set the level of equivalence at -5 percent difference between (KK2.0 –KK1.0), a negative value indicating that KK1.0 is better.

*5*.*1*.*1 Diagnostic performance*. For the clinical sensitivity to detect low intensity (***H1*.*1***) and MHI infections (***H1*.*2***), we accounted for (i) a varying clinical sensitivity as a function of the number of eggs in a slide; (ii) a proportion of the eggs in a slide being missed, (iii) correlation between test results of KK1.0 and KK2.0 on the same slide, (iii) and helminth specific FEC thresholds defining low intensity and MHI infections (**Table 5**). In this simulation, we assumed that the clinical sensitivity of KK2.0 is equal to that of KK1.0 and an equivalence level of 5-point percent. In other words, the lower limit of the CI around the difference (KK2.0 –KK1.0) should be at least -5% (see also **Fig 5**). As we will draw conclusions on three different STHs at the same time and because we are testing for non-inferiority, we set the level of significance at 0.05/3.

**Table 5 pone.0309816.t005:** The FEC thresholds defining low intensity and MHI STH infections. This table summarizes the WHO FEC (in EPG) thresholds to classify the intensity of STH infections into low, moderate and heavy [44].

Helminth	Low	Moderate	Heavy
*Ascaris*	1–4,999	5,000–49,999	≥50,000
*Trichuris*	1–999	1,000–9,999	≥10,000
Hookworm	1–1,999	2,000–3,999	≥4,000

Based on these assumptions, the required number of KK thick smears representing low intensity infections based on the ground truth is 125 for *Ascaris*, 180 for *Trichuris* and 140 for hookworms. The required number of KK thick smears representing MHI infections based on the ground truth, is 110 for *Ascaris* and 145 for *Trichuris*. For hookworms, the required sample size exceeded 350, which revealed to be beyond the capacity of this project.

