**Methods:**

Here, we describe the study protocol for a comprehensive evaluation of the AI-DP based on its (i) diagnostic performance, (ii) repeatability/reproducibility, (iii) time-to-result, (iv) cost-efficiency to inform large-scale deworming programs, and (v) usability in both laboratory and field settings. For each of these five attributes, we designed separate experiments with sufficient power to verify the non-inferiority of the AI-DP (KK2.0) over the manual screening of the KK stool thick smears (KK1.0). These experiments will be conducted in two STH endemic countries with national deworming programs (Ethiopia and Uganda), focussing on school-age children only.

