### 4 The experiments to comprehensively evaluate KK2.0

This comprehensive evaluation consists of five experiments, each one designed to evaluate one of the five attributes: (i) diagnostic performance, (ii) repeatability/reproducibility, (iii) time-to-result, (iv) cost-efficiency to inform large-scale deworming programs, and (v) usability in both a laboratory and field setting. **Table 3** provides an overview of the hypotheses, the primary and secondary outcomes for each experiment separately. Across these five experiments, we defined nine hypotheses, 13 primary and 17 secondary outcomes. Generally, we hypothesize that KK2.0 is non-inferior to KK1.0. Note that a hypothesis was not defined for both the time-to-result and usability experiments. This was because the outcomes of the time-to-result experiment will feed into the experiment on cost-efficiency and because the usability experiment was designed to gain insights into how we can further improve the usability of KK2.0 only. In the following sections we will discuss each experiment in detail. The sample size calculation and the statistical data analysis will be discussed in **section 5**.

**Table 3 pone.0309816.t003:** An overview of the hypotheses, primary, and secondary outcomes to comprehensively evaluate KK2.0.

Experiment	Hypotheses			Primary outcomes		Secondary outcomes
1) Diagnostic performance	**H1.1**	the clinical sensitivity of KK2.0 to detect low intensity infections is non-inferior to that of KK1.0 for *Ascaris*, *Trichuris* and hookworms	**P1.1**	the clinical sensitivity of KK2.0 and KK1.0 to detect low intensity infections of *Ascaris*, *Trichuris* and hookworms	**S1.1**	the clinical sensitivity and clinical specificity of KK1.0 and KK2.0 to detect *S*. *mansoni* infections
	**H1.2**	the clinical sensitivity of KK2.0 to detect MHI infections is non-inferior to that of KK1.0 for *Ascaris*, *Trichuris* and hookworms	**P1.2**	the clinical sensitivity of KK2.0 and KK1.0 to detect MHI infections of *Ascaris*, *Trichuris* and hookworms	**S1.2**	the detection limit (the lowest number of eggs that yields a positive test result in 95% of the cases) for both KK1.0 and KK2.0, and *Ascaris*, *Trichuris*, hookworm, and *S*. *mansoni* separately

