### 6 Statistical data analysis

#### 6.1 Diagnostic performance

*6*.*1*.*1 Primary outcomes*. We will draw contingency tables representing the test results of both KK1.0 and KK2.0 for each type of ground truth (no, low intensity and MHI infections) and STH species (*Ascaris*, *Trichuris* and hookworms). From these tables, both the clinical sensitivity and specificity, and the corresponding 95% CI (Wald) will be calculated for each test and STH separately. Subsequently, we will also calculate the 90% CI around the difference in performance (KK2.0-KK1.0) accounting for multiple hypotheses testing. Given that test results are paired (same smears are processed by KK1.0 and KK2.0, we will use the formulae described by Newcombe for paired data [46]. We will conclude that the clinical sensitivity or specificity of KK2.0 for a particular STH is non-inferior if the lower limit of the adjusted 90% CI does not include the -5-point percent.

*6*.*1*.*2 Secondary outcomes*. We will draw contingency tables representing the test results of both KK1.0 and KK2.0 for each type of ground truth for *S*. *mansoni* infections. From these tables, both the clinical sensitivity and specificity, and the corresponding 95% CI will be calculated (***S1*.*1***).

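### Hookworm moderate-to-heavy intensity sensitivity stays a confirmatory comparison in H1.2 although section 5.1.1 puts its sample size out of reach, so the power and spiking statements need qualifying

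*Protocol article*

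**What the plan says.** H1.2 in Table 3 reads: "the clinical sensitivity of KK2.0 to detect MHI infections is non-inferior to that of KK1.0 for *Ascaris*, *Trichuris* and hookworms". P1.2 makes the matching sensitivities a primary outcome, and Table 4 repeats the hypothesis with 110 MHI smears for *Ascaris*, 145 for *Trichuris* and more than 350 for hookworm.

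Section 5.1.1 assumes equal sensitivity of the two methods and sets the criterion that "the lower limit of the CI around the difference (KK2.0 –KK1.0) should be at least -5" percent. It divides alpha by three, to 0.05/3, because a conclusion is wanted for each of the three species. Section 5.1 sets the power target at 80%. Section 5.1.1 then reports for the MHI comparison: "For hookworms, the required sample size exceeded 350, which revealed to be beyond the capacity of this project".

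Section 6.1.1 says "we will also calculate the 90% CI around the difference in performance (KK2.0-KK1.0) accounting for multiple hypotheses testing", and concludes non-inferiority for a given species when the lower limit clears -5 points. It makes no exception for hookworm.

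Two other places describe the design more favourably. Referring to all five attributes, the Abstract (Methods) says "we designed separate experiments with sufficient power to verify the non-inferiority of the AI-DP (KK2.0) over the manual screening". Section 4.1 gives, as the reason for egg spiking, that enough MHI infections will be obtained for each of the three species.

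**The concern.** The plan states a limitation and does not carry it through. Having found the hookworm MHI sample size infeasible, it neither makes that comparison descriptive nor says how many hookworm MHI smears it expects or what power they would give. The formal rule will still return a hookworm verdict on a primary outcome. If KK2.0 is truly as sensitive as KK1.0, that verdict may well be a failure to show non-inferiority simply because the interval is wide.

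This matters because MHI prevalence below 2% is the elimination milestone that the Introduction cites, and the Abstract says the data will be used to seek WHO approval. A reader who relies on the Abstract and section 4.1 would assume that the hookworm comparison had been adequately sized.

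**Working it through.** **Does the text provide for the shortfall?**

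| Place | Treatment of hookworm MHI sensitivity |
|---|---|
| Table 3, H1.2 and P1.2 | Included with the other two species |
| Table 4 | Listed, more than 350 smears |
| Section 5.1.1 | Required number beyond capacity; alpha divided by three |
| Section 6.1.1 | Same non-inferiority rule, no exception |
| Section 4.1 | Spiking said to give enough MHI cases for each species |
| Abstract | Sufficient power, no qualification |

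Nothing in the article makes the comparison descriptive or gives a planned number.

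**Does the Abstract's statement hold for the five attributes?** Section 4 says "a hypothesis was not defined for both the time-to-result and usability experiments". Section 5 gives no sample size for cost-efficiency, whose hypotheses rest on simulation. Sections 5.1.2 and 6.2.1 test repeatability and reproducibility against fixed percentages (99% assumed, 95% as the bound), not against KK1.0. A powered non-inferiority comparison with KK1.0 therefore exists only for diagnostic performance, and there not for hookworm MHI.

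**How large is the shortfall?**

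*Inputs from the article:* margin 0.05; true difference 0; power 80%; alpha 0.05/3; requirement above 350.

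*Assumptions:* the adjusted 90% interval is read as one-sided 0.05/3. The simulation inputs are in S3 File, which is not shown, so the figure above 350 cannot be reproduced and is not disputed. Instead, the proportion of discordant smears ψ is back-solved from it.

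1. Paired normal approximation: n = ψ(z₁₋α + z₀.₈)² / 0.05².
2. z₁₋α = 2.128 and z₀.₈ = 0.842. The sum is 2.970 and its square 8.819.
3. At n = 350: ψ = 350 × 0.0025 / 8.819 = 0.0992. The true requirement is larger, so ψ is at least this and the powers below are upper bounds under the approximation. For comparison, 110 and 145 smears imply ψ of 0.031 and 0.041.
4. Power = Φ(0.05√(n/ψ) − 2.128), which equals Φ(2.970√(n/350) − 2.128).

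| Hookworm MHI smears (assumed) | Argument of Φ | Power, at most about |
|---|---|---|
| 110 | −0.463 | 32% |
| 145 | −0.217 | 41% |
| 200 | 0.117 | 55% |
| 250 | 0.382 | 65% |
| 300 | 0.621 | 73% |

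*Cross-check:* simulating the Newcombe paired interval that section 6.1.1 names (40,000 runs, ψ = 0.10, sensitivity 0.70 to 0.95) gives 25–30% at 110, 34–40% at 145, 49–53% at 200 and 77–79% at 350.

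*Other reading of alpha:* with one-sided 0.05/6, z₁₋α = 2.394 and the sum is 3.236. Power is then Φ(3.236√(n/350) − 2.394): 28% at 110, 38% at 145 and 73% at 300. The picture is the same.

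**What does the three-way alpha split cost?** *Ascaris* and *Trichuris* are sized for 80% power at 0.05/3. At 0.05/2 (z = 1.960) with the same numbers, power is Φ(2.970 − 1.960) = Φ(1.010) = 84%. Equivalently, the required numbers scale by (1.960 + 0.842)² / 8.819 = 0.890, to about 98 and 130.

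**The case against.** The shortfall is disclosed: section 5.1.1 states it and Table 4 prints it, so nothing is concealed. S3 File may give a planned hookworm number. Both points stand. Even so, the decision rule and the two broad statements are in the article itself and conflict with section 5.1.1 as written.

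A reader might infer that H1.2 as a whole cannot succeed because it names three species. The article does not support this. Section 6.1.1 concludes species by species, and an alpha split makes sense only for separate claims.

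A reader might also infer that the hookworm test cannot succeed. What is beyond capacity is the number needed for 80% power; power falls short but is not zero. Nor is a failed test formally a finding of inferiority: the Fig 5 caption treats it as absence of evidence for non-inferiority, and the interval for the difference will be calculated, so imprecision would be visible. That softens the harm. It does not justify a confirmatory verdict whose failure would be largely uninformative.

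Finally, a reader might take the division of alpha by three as an error. It is valid and conservative, and its cost is small.

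**Conclusion.** The point holds for one of the twelve species-by-hypothesis comparisons in H1.1 to H1.4. Hookworm MHI sensitivity is kept confirmatory without the sample size that the plan says it needs, and the Abstract's power claim and the section 4.1 spiking statement are not true for it. Separately, the Abstract's claim is too broad for the other four attributes.

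Hookworm power is below the 80% target at any number up to 350: at most about 32% at 110 smears, rising to about 73% at 300. No single figure can be given as the plan's power, because no planned number appears in the article. The range rests on a back-solved discordance and a normal approximation, both chosen or checked as above. Type I error is not threatened, and the *Ascaris* and *Trichuris* conclusions stand on their own.

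**What to change.** 1. In Tables 3 and 4 and sections 5.1.1 and 6.1.1, report hookworm MHI sensitivity for both methods and their difference as estimates with confidence intervals, without a non-inferiority conclusion. Alternatively, keep the test, state the planned number of hookworm MHI smears and the power it gives, and call it underpowered.
2. Limit the Abstract's power statement to H1.1, H1.2 for *Ascaris* and *Trichuris*, H1.3 and H1.4 and, against their fixed threshold, H2.1 to H2.3, which have a formal 80% power calculation in section 5.1.2.
3. Qualify the section 4.1 sentence so that it no longer promises enough MHI cases for hookworm.
4. Optional: if hookworm leaves the H1.2 family, test *Ascaris* and *Trichuris* at 0.05/2.

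These are wording changes with no extra samples or procedures. The only thing given up is a confirmatory claim for which the protocol already says it cannot reach the sample size.

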#### 5.2 Usability

In this experiment, we will include 16 participants to receive (i) practical training and engage in the three-step process (ii–iv) and usability testing. A group size of 3–20 participants is considered valid in such problem discovery scenarios, with 5–10 participants being a sensible baseline range [45]. The group size should typically be increased along with the study’s complexity and the criticality of its context. Since the study will take place in two different settings, either in a well-equipped laboratory or field setting, we considered 8 participants per setting, resulting in a total of 16 participants (4 groups of 2 participants per setting).

### 6 Statistical data analysis

#### 6.1 Diagnostic performance

*6*.*1*.*1 Primary outcomes*. We will draw contingency tables representing the test results of both KK1.0 and KK2.0 for each type of ground truth (no, low intensity and MHI infections) and STH species (*Ascaris*, *Trichuris* and hookworms). From these tables, both the clinical sensitivity and specificity, and the corresponding 95% CI (Wald) will be calculated for each test and STH separately. Subsequently, we will also calculate the 90% CI around the difference in performance (KK2.0-KK1.0) accounting for multiple hypotheses testing. Given that test results are paired (same smears are processed by KK1.0 and KK2.0, we will use the formulae described by Newcombe for paired data [46]. We will conclude that the clinical sensitivity or specificity of KK2.0 for a particular STH is non-inferior if the lower limit of the adjusted 90% CI does not include the -5-point percent.

*6*.*1*.*2 Secondary outcomes*. We will draw contingency tables representing the test results of both KK1.0 and KK2.0 for each type of ground truth for *S*. *mansoni* infections. From these tables, both the clinical sensitivity and specificity, and the corresponding 95% CI will be calculated (***S1*.*1***).

To determine the detection limit (the lowest number of eggs that yields a positive test result in 95% of the cases) of KK1.0 and KK2.0 for STH and *S*. *mansoni* (**S1.2**), logistic regression models accounting for repeated measures will be built for each helminth species separately using the ‘mixed_model’ function in R. The test result (positive or negative) will be used as dependent variable while ‘test’ (2 levels: ‘KK1.0’, ‘KK2.0’), log transformed egg counts based on ground truth at first examination, Bristol stool scale and all two-way interactions will be used as predicting variables. From these models, we will predict the probability having a positive test result and the corresponding 95% prediction interval for each integer value of ground truth egg counts between 1 and 100 using the ‘marginal_coefs’ function in R. We will define the detection limit as that range of egg counts for which the 95% prediction intervals include 0.95. We will explore the egg recovery rate (= observed egg counts / ground truth egg counts) of KK1.0 and KK2.0 when compared to the ground truth for *Ascaris*, *Trichuris*, hookworms and *S*. *mansoni* (***S1*.*3***). These analyses will only be conducted on KK thick smears representing low intensity infections. Finally, we will draw contingency tables representing the test results of KK2.0 for each type of ground truth (negative, low intensity and MHI infections) for each helminth species and AI verification process (simplified AI verification (limited selection of AI objects presented for verification) *vs*. no AI verification), separately. From these tables, both the clinical sensitivity and specificity, and the corresponding 95% CI will be calculated for each helminth species and type of AI-verification process (***S1*.*4***).

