#### 4.1 Diagnostic performance

**Fig 3** provides an overview of the proposed study design for the experiment on the diagnostic performance. Generally, this experiment consists of five consecutive steps, with the second step offering two methods to validate diagnostic performance. The first method involves verifying egg counts by reviewing and counting all eggs within the captured FOVs. The second method entails spiking a minimum number of eggs into randomly selected stool samples to achieve counts indicating an MHI infection. In the **first step** of the experiment, fresh stool samples will be collected from SAC at the schools. In the **second step**, the consistency of the stool samples will be scored based on the Bristol Stool Chart [38]. Subsequently, sample will be homogenised, and one KK thick smear per sample will be prepared in one of the two following ways for the two validation methods described above. For FOV-based validation (**step 2A**), samples will be processed as recommended by WHO. For egg spiking-based validation (**step 2B**), the cone of stool (after removing the KK template) will be spiked with purified eggs to artificially increase the egg counts to at least an MHI infection (*Ascaris*: >209 eggs; *Trichuris*: >42 eggs; hookworms: >84 eggs). This step 2B will only be done in a subset of the samples (never on samples that are processed through 2A) and is introduced to ensure that sufficient cases of MHI infections for each of the STHs are obtained (see also **section 5**). The selection of the samples to be spiked will be done through a randomization process. In the **third step** and following a smear clearing time of 30 min, the smears will be randomly allocated to be analysed by either KK1.0 (even participant ID) or KK2.0 (odd participant IDs). This randomization process is required to avoid systematic bias due to hookworm egg degradation over time [13, 14, 39]. In the **fourth step**, egg counts will be recorded for each helminth species (*Ascaris*, *Trichuris*, hookworm and *S*. *mansoni*), separately. Thereafter (**step 5**), KK thick smears will be stored at 4°C to be used in the context of the experiment on reproducibility/repeatability (see **section 4.2**). In Ethiopia, sample processing (from step 2 onwards) will be conducted in the Neglected Tropical Disease Laboratory of Jimma University (a fully equipped laboratory setting), while in Uganda all steps will be conducted on-site (M&E setting).

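### Section 6.1.2 defines the detection limit (S1.2) as a range of egg counts, which contradicts the single lowest count declared in Table 3 and in its own opening sentence

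*Protocol article*

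**What the plan says.** Table 3 of the protocol article lists S1.2 as the detection limit of each test for *Ascaris*, *Trichuris*, hookworm and *S. mansoni* separately, and explains it as "the lowest number of eggs that yields a positive test result in 95% of the cases". This is a single count.

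Section 6.1.2 opens its description of the analysis with the same meaning: "To determine the detection limit (the lowest number of eggs that yields a positive test result in 95% of the cases". It plans a logistic model with repeated measures for each species, with test, log ground-truth egg count, Bristol score and all two-way interactions as predictors. Probabilities of a positive result, with 95% intervals, are predicted "for each integer value of ground truth egg counts between 1 and 100".

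The rule for reading off the result follows: "We will define the detection limit as that range of egg counts for which the 95% prediction intervals include 0.95".

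After a sentence on egg recovery (S1.3), the paragraph adds: "These analyses will only be conducted on KK thick smears representing low intensity infections". The text does not say whether this covers S1.2 and S1.3 or S1.3 alone.

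**The concern.** One outcome carries two definitions that cannot both be applied. The declared quantity is a property of the test. The quantity that section 6.1.2 would report is the set of counts at which 0.95 cannot be excluded, so it also reflects how many smears were read. An analyst who follows the rule literally does not produce the outcome in Table 3. A reader who takes the bottom of the range as the lowest detectable count will credit the test with more than the fitted curve shows.

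A second, conditional matter is the prediction grid. It is the same for every species, although low intensity *Trichuris* and hookworm smears cannot reach 100 eggs.

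**Working it through.** **1. The definitions side by side.** Table 3 and the opening of the S1.2 text give the smallest count x with P(positive | x) = 0.95. The later rule gives all x with lower limit(x) ≤ 0.95 ≤ upper limit(x). The second is the usual inversion set, that is, an interval for the first. At its smallest member the upper limit has only just reached 0.95, so the predicted probability there is below 0.95.

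**2. How the range behaves.** The protocol gives no numeric detection limit and no sample size for S1.2, so this step is illustrative. It takes the low intensity smear numbers planned for H1.1 (section 5.1.1: 125 *Ascaris*, 180 *Trichuris*, 140 hookworm), then four and sixteen times as many.

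Assumptions not in the document:
- logit p(x) = ln 19 + b·ln(x/L), so that p(L) = 0.95 (0.95/0.05 = 19);
- one test, no random effect and no Bristol term;
- counts log-uniform up to the low intensity ceiling;
- a 95% Wald interval on the fitted probability, and 300 runs per setting.

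With L = 20 eggs and b = 1.0:

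| Species | Smears | Median single-value estimate | Median range under the 6.1.2 rule |
|---|---|---|---|
| *Ascaris* | 125 | 18.7 | 10 to 100 |
| *Ascaris* | 500 | 19.9 | 13 to 38 |
| *Ascaris* | 2,000 | 20.1 | 16 to 26 |
| *Trichuris* | 180 | 19.3 | 11 to 73 |
| *Trichuris* | 720 | 19.6 | 14 to 32 |
| *Trichuris* | 2,880 | 20.0 | 17 to 25 |
| Hookworm | 140 | 19.0 | 10 to 92 |
| Hookworm | 560 | 20.2 | 14 to 36 |
| Hookworm | 2,240 | 20.0 | 16 to 26 |

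The true curve is the same in every row. With b = 1.5 the ranges at the planned numbers are narrower (12 to 60, 13 to 42 and 12 to 46). Over both slopes the single-value estimate lies between 18.7 and 20.4.

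True detection at the lower ends, with b = 1.0:
- *Trichuris*, 11 eggs: odds 19 × 11/20 = 10.45, so p = 10.45/11.45 = 0.913.
- *Ascaris* and hookworm, 10 eggs: odds 19 × 10/20 = 9.5, so p = 9.5/10.5 = 0.905.

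**3. The grid against the data, if the low intensity restriction covers S1.2.** Section 4.1 (step 2B) gives egg counts for moderate-to-heavy infection: *Ascaris* >209 and "Trichuris*: >42 eggs; hookworms: >84 eggs". Table 5 starts moderate infection at 5,000, 1,000 and 2,000 EPG. The EPG-per-egg factor is not printed, but 24 is the only integer that reproduces all three counts by rounding up:
- 5,000/24 = 208.3 → 209
- 1,000/24 = 41.7 → 42
- 2,000/24 = 83.3 → 84

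Low intensity smears therefore hold at most 208, 41 and 83 eggs. Grid points above the ceiling:
- *Ascaris*: 0
- *Trichuris*: 100 − 41 = 59
- hookworm: 100 − 83 = 17

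If the step 2B signs are read literally, the last two become 58 and 16. Table 5 has no row for *S. mansoni*, so no ceiling can be derived.

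Whether the reported range itself passes a ceiling depends on the curve. Over L = 10, 20 or 40 and b = 1.0 or 1.5, at the planned numbers, it did so in 8% to 96% of runs for *Trichuris*, 4% to 79% for hookworm and never for *Ascaris*. A separate 400-run check for *Trichuris* with L = 10 gave 53% at b = 1.0, 7.5% at b = 1.5 and 0% at b = 2.0.

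**The case against.** The strongest defence is that both definitions aim at the same point on the curve. The range is a standard interval for that point, and the planned output already contains the predicted probability at every count, so the single value can be read off. On this view the fault is one of labelling. That is largely right, and it is why the repair is small. It does not remove the contradiction, because the text states explicitly that the range is the detection limit. This is not a detail left open for an analysis plan to settle.

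Three stronger readings might be inferred, and the document does not support them.

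- *The comparison of KK1.0 with KK2.0 is distorted by unequal precision.* Section 6.1.1 says the same smears are processed by both tests, and section 6.1.2 puts both into one model with a test term. Sample size and egg-count distribution are therefore shared. Range widths may still differ because the curves differ, but not because one test has fewer smears. S1.2 also has no hypothesis, margin or decision rule.
- *The reported limit extends beyond the data.* The sentence on low intensity smears directly follows S1.3 and may apply to S1.3 only. Even on the wider reading, only the grid certainly passes the ceiling, and only for *Trichuris* and hookworm. *Ascaris* is never affected, and *S. mansoni* has no stated ceiling.
- *The simulated widths forecast this trial.* The slopes, true limits and count distribution are assumed, and the model is simpler than the planned one. High extrapolation rates at a shallow slope are a feature of that scenario, not of the protocol.

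**Conclusion.** The point holds as a contradiction of definition. Section 6.1.2 conflicts with Table 3 and with its own opening sentence, and the rule as written does not return the declared outcome. This part rests on the text alone. That the range depends on precision and includes counts with predicted detection below 95% follows from how it is constructed; the simulation only illustrates the possible size.

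The grid matter is conditional. It applies if the low intensity restriction covers S1.2, and then to *Trichuris* and hookworm, with ceilings of about 41 and 83 eggs that rest on the inferred factor of 24. Whether a reported range would cross them cannot be known before the detection curve is.

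The consequence is minor. S1.2 is secondary, and the primary non-inferiority conclusions do not depend on it.

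**What to change.** In section 6.1.2, define the detection limit for each test and species as the smallest egg count whose predicted marginal probability of a positive result is at least 0.95. Report the range now described as the 95% interval for that limit. Table 3 can stay as it is.

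State whether the restriction to low intensity smears applies to S1.2. If it does, limit the predictions to the observed counts for *Trichuris* (at most about 41 eggs) and hookworm (at most about 83). If 0.95 is not reached within the observed counts, report the limit as lying above the largest of them.

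An estimate of the KK2.0 minus KK1.0 difference in detection limits would be an optional extra analysis; Table 3 does not promise one and the correction does not need it.

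The cost is a change of wording. The model, data and sample size stay the same.
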